## **Background.**

**The incidence rates for most cancers have increased significantly** in all Western countries over the last decades. Comparing age-adjusted incidence rates for some major cancer forms during the time period of 1959-63 versus 2014-18 in Norway, cancer of the colon and rectum increased by about 150% in both sexes, testicular cancers by 200%, brain tumours by 150%, while breast and prostate cancer both increased by more than 100% (Norwegian Cancer Registry; [https://www.kreftregisteret.no/Registrene/Kreft\\_i\\_Norge/](https://www.kreftregisteret.no/Registrene/Kreft_i_Norge/)). Within the same time-span, there has been a 9-fold increase in melanoma incidence and a 10-fold increase in lung cancer incidence in females. These increased incidences are likely due to changes in UV-light exposition and smoking habits. In addition, a reduction of 85% in stomach cancer is likely related to better-preserved food. Importantly, however, for most major cancer forms we lack an explanation for the increased incidence. While factors like an increase in obesity rates have been linked to cancer incidence, this presents by no mean the full explanation. Notably, immigration studies from different countries have revealed a strong impact on cancer risk in second-generation immigrants (1-4), indicating environmental influence to be of key importance.

Occupational exposure to toxic agents (asbestos, benzene and many environmental pollutants) are known to increase cancer risk. However, while a general opinion is that increased risk of many cancers in the western population may be due to environmental influences like food ingestion and different types of exposure to polluting agents, in general we lack direct evidence linking enhanced cancer risk to defined factors. Moreover, we have limited knowledge regarding molecular mechanisms by which polluting agents may induce distinct cancer forms. While defined toxic agents (like cigarette smoking and UV exposure) are associated with distinct genomic signatures, reflecting physical or chemical damage on DNA in certain cancer forms (5), as for most cancer forms defined mutation signatures related to exogenous agents have not been identified.

**Genetic silencing by epigenetic regulation** is part of multiple normal physiological processes and plays a pivotal role during embryogenesis. Gene promoter regions, in general

located within a thousand base pairs upstream of the gene, are typically characterized by a high density of CpG dinucleotides into so-called CpG islands (6). Epigenetic regulation involves at least two different processes, CpG methylation, and histone demethylations (7). These two events in general appear in concert (8), making CpG methylation a suitable marker of epigenetic silencing of many genes. Abnormal epigenetic regulation is coined epimutations and may occur *in utero*, so-called **constitutional epimutations**, or in different tissues later in life as **somatic epimutations**. The fact that epigenetic regulation is influenced by genetic but also environmental factors including pollutants (9-14) makes **epimutations** strong candidates linking environmental agents to cancer risk.

**Constitutional epimutations** presents epigenetic disturbances arising *in utero*, normally affecting tissues belonging to all three germ layers (15, 16). **Constitutional methylations** are classified into two major groups; **primary epimutations** where no associated DNA sequence variant is detected, and **secondary epimutations**, occurring as a consequence of a local *cis*-acting DNA alteration (17, 18). While gene silencing through somatic epimutations are frequently observed in cancer tissue (19), despite some preliminary reports (evidence summarized in (20)), very few studies have investigated constitutional epimutations as potential underlying causes in carcinogenesis. Carcinogenesis evolve over time, including early life events (21) and for certain cancer forms, indirect evidence points toward prenatal events to be of importance for later carcinogenesis (22).

While secondary constitutional epimutations in tumor suppressor genes like *MLH1*, *BRCA1* and *MSH2* (11, 23-26) have been associated with elevated cancer risk, such secondary epimutations are extremely rare (20). Notably, secondary epimutations in general are easily detected due to the fact that they typically affect approximately 50% of the alleles. In contrast, while primary epimutations seems to occur more frequently, they may easily be overlooked due to a low-mosaic expression (27).

### **Evidence supporting mosaic methylation may be a cancer risk factor.**

In a previous study, enrolling more than 4.000 patients diagnosed with high-grade serous ovarian cancer (HGSOC) and controls (27), we found low-mosaic *BRCA1* WBC methylation in 4-7% of healthy newborns (umbilical blood) as well as adults. In adult women, WBC methylation was associated with a 2.2 – 2.9 OR for HGSOC. A potential bias of that study, like all the other studies in this area (27-30), was the collection of blood samples after diagnosis.

**To avoid the bias of tumor-related effects on WBC methylation, we recently assessed *BRCA1* methylation status in WBC DNA collected from >5.000 women in the American Women Health Initiative (WHI) study (31) out of whom about 660 later developed triple negative breast cancer (TNBC) and 550 high-grade serous ovarian cancer (HGSOC), in a case-control design study.** The results showed a significant elevated OR both for incidental TNBC and HGSOC, even in sub analyses limited to women developing their cancers >5 years after WBC sampling (paper submitted). The results for TNBC is revealed below:

[figure not shown]

**This, for the first time, confirms normal tissue methylation to be predictive of subsequent cancer development in a prospective setting. Moreover, *BRCA1* promoter methylation occurred as a monoallelic event, in affected individuals, consistent with early origin of the methylation, followed by clonal expansion.**

Finally, the fact that mosaic germline mutations may confer risk of cancers as well as other medical conditions (32-39) supports the hypothesis that mosaic epimutations may confer risk of disease as well.

## Study Approach.

**One approach** searching for novel cancer risk factors is to assess alternative inactivation mechanisms for genes in which germline mutations are strongly associated with cancer. **We have already applied this approach successfully by identifying methylation of the *BRCA1* gene as a risk factor for breast and ovarian cancer (see below). There are other candidate for which epimutations may be a potential cancer initiating factor.** Lynch Syndrome is an autosomal dominant genetic condition caused by germline mutations in genes regulating DNA mismatch repair defects (*MLH1*, *MSH2*, *MSH6*, *PMS1* or *PMS2*) (40). The syndrome is characterized by an elevated risk of colorectal and endometrial cancer as well as several other cancer forms, and the tumors characteristically express so-called microsatellite instability; MSI) (41-44) While the Lynch syndrome accounts for only 2-3% of all colon cancers (45, 46), up to 15% of all colon cancers are defined as MSI+ and the majority of these MSI+ colon cancers carries methylation of the *MLH1* promoter (47-52). This, together with the finding of *MLH1* methylation in adjacent normal colon tissue (51) indicates *MLH1* methylation to be an early event in carcinogenesis. In endometrial cancers, about 30% are found to harbor methylation of the *MLH1* gene promoter (53, 54). While secondary *MLH1* epimutations and high-VAF *MLH1* epimutations without genomic defects have been reported in association with MSI+ colon cancer, (23-25, 55-66), to this end a total of less than 50 individuals have been reported in the literature. In contrast, while low-level mosaic WBC methylation of *MLH1* in patients with colorectal cancer has been reported (56, 63), the potential implications of such low-level methylation to colorectal cancer risk has not been formally assessed. While constitutional methylation of *MSH2* has been described in a few families (11, 66, 67), these epimutations all are secondary due to a deletion in the *TACSTD1* gene located upstream of *MSH2*.

However, there is evidence suggesting normal colon (and probably other tissues as well) methylation of the *MLH1* gene to be an acquired event during lifetime. Many colon cancers are known to carry promotor methylation of different genes, partly in concert, in the so-called CIMP phenotype, and much of this methylation arise in an age-dependent manner (68-70). The

time-point when *MLH1* methylation occurs remains unsettled. Most importantly, studying low-level mosaic methylation in WBC from newborns, we found *MLH1* promoter methylation to occur in less than 0.5% of individuals only. While this finding does not exclude an organ-specific embryonic origin of methylation of normal colon cells, such an event must have happened after separation of the primordial layers (colon = endodermal derived), excluding a model using WBC methylation as a potential surrogate marker for constitutional methylation of endodermal derived tissue.

**A second approach** is to look for tumor suppressor genes frequently methylated across a panel of cancer forms, like the *MGMT* gene (71). *MGMT* is pivotal to O-methylguanine detoxification. The importance of this mechanism is illustrated by loss of *MGMT* expression being associated with sensitivity towards alkylating chemotherapeutics (72). *MGMT* is downregulated by promoter methylation in various types of cancers like colon cancer, glioblastomas and diffuse large B-cell lymphomas, affecting 20-40% of all tumors in all three groups (72-78).

Most importantly, findings by us (>1,000 newborns studied) and others (79) have detected mosaic *MGMT* promoter methylation in white blood cells (WBC) in about 15% of newborns. Thus, constitutional methylation of *MGMT*, similar to *BRCA1*, is an embryonic event affecting a significant number of individuals. **Importantly, in case we may confirm an association between *MGMT* methylation and cancer risk, this may indicate a key role of specific genotoxic events in the carcinogenic process of the actual tumors (71).**

For most genes, we lack detailed knowledge about exactly which CpG's in the promoter area that needs methylation to cause transcription silencing. Moreover, we lack knowledge whether promoter methylation always develops as a “one-step-process” (as outlined in model A and B in Figure 1) or may develop stepwise (model C in Figure 1) for which there is some indirect evidence (80-83). Notably, while in our study of the *BRCA1* gene, we found a methylation pattern consistent with model A, this by no means excludes the possibility of different patterns among other genes subject to constitutional methylation. In the present study of *MGMT* methylation, in addition to evaluating the cancer hazard ratios (HR) related to elevated methylation status defined by Variant Epiallele Frequency (VEF; as in our previous study), we will conduct extensive formal assessment of these models based on data generated by Next-Generation Sequencing (NGS) technology.

[figure not shown]

**Figure 1.** Examples of different models for organ-specific effects of constitutional methylation. A: **Clonal expansion**, B: **Critical CpG methylation**: some CpGs are critical to gene silencing, C: **Dynamic methylation**; promoter methylation may evolve as a step-wise process

## **MGMT methylation in cancer.**

*MGMT is a tumor suppressor, pivotal to O-methylguanine detoxification, downregulated by promoter methylation in various types of cancers like colon cancer and glioblastomas affecting 30-40% of all tumors in both groups. Preliminary findings by us and others (79) have detected MGMT promoter methylation in WBC in about 15% of newborns.* About 30-40% of all colon cancers but also colon polyps, acting as pre-cancer lesions, as well as other cancer forms like glioblastomas reveal hypermethylation of the *MGMT* promoter (72-78). Notably, *MGMT* methylation has been associated with sensitivity towards alkylating chemotherapeutics (72, 84, 85). While germline pathogenic mutations in the *MGMT* gene have not been reported, the T-allele of the SNP rs16906252, located close to the transcription start site in the first exon of *MGMT*, has been associated with elevated promoter methylation across a panel of solid malignancies (73, 86-90). *MGMT* methylation however has been detected in normal colon mucosa located 10 cm from the tumor borders (91), questioning the possibility of tissue-specific methylation. There may be several explanations for this finding, including local clonal expansion of constitutional methylated cells as a pre-cancer stage. Thus, we (unpubl observations) and others (92) have detected mosaic *MGMT* methylation in WBC in > 15% of newborns.

For the present project, we selected colon cancers and glioblastomas to assess potential impact of *MGMT* constitutional methylation status on cancer HR. In addition, we searched the literature for a potential third cancer type suitable for this project. The requirements were a) a cancer form for which a suitable fraction of tumors are found methylated at the *MGMT* promoter, and b) the number of participants in the WHI diagnosed with this cancer form should allow for statistical testing of HR based on upfront power estimates. Based on these criteria, we selected diffuse large B-cell lymphomas, a tumor form for which between 20 and 40% of the tumors have been reported methylated for the *MGMT* gene (88, 93-96). Regarding numbers, >500 cases have been diagnosed in the WHI data-set.

Assessing *MGMT* epimutations as a potential cancer risk factor would address several important questions. First, the fact that it specifically detoxifies O-methylguanine would link *MGMT* inactivation to a specific mechanism of carcinogenesis (71). Next, it may present the first gene acting as a cancer risk factor through constitutional epimutations for which germline mutations have not been detected. Third, assessing the SNP variant in concert with epimutation status, *MGMT* could be a gene for which both primary and secondary epimutations may be assessed separately and/or in concert as cancer risk factors. Forth, and most important: the three tumours selected represent a spectrum of different tumor forms in respect to biology and hypothesis on carcinogenesis in general. Colon cancer has been strongly associated with diet, indicating local exposure to the epithelial lining could play an important role. Thus, an interaction between *MGMT* deactivation in epithelial lining cells and carcinogen exposure may be hypothesized. As for glioblastomas and high-grade lymphomas, potential risk factors remain unknown. Finally, the fact that these three cancers originate from tissue derived from all the three different germ layers (colon: endoderm, glioblastomas; ectoderm, and lymphomas: mesoderm) make these three cancer forms in concert of interest, considering the fact that constitutional methylations in general may affect all three germ-cell layers.

## **Current study.**

**Here, we will confirm constitutional primary epimutations of *MGMT* to be a cancer risk factor by evaluating WBC *MGMT* methylation as risk factor for colorectal cancer, glioblastomas and high-grade lymphomas.** Data generated will be used also to model the mechanism(s) of CpG methylation building up across the promotor area, evaluating the different models outlined in Figure 1.

### Specific aims.

1. We will assess the HR for right-sided and left-sided colon cancer separately related to WBC *MGMT* methylation status using a case-control designed study
2. We will assess the HR for glioblastoma multiforme related to WBC *MGMT* methylation status using a case-control designed study
3. We will assess the HR for high-grade diffuse B-cell lymphomas related to WBC *MGMT* methylation status using a case-control designed study

### Significance of findings.

The findings of this study may have three major implications. First, it may add pivotal evidence to our understanding of the mechanism of carcinogenesis. In our previous study we found primary constitutional mosaic epimutations in the *BRCA1* gene to be associated with subsequent risk of triple-negative breast cancer and high-grade serous ovarian cancer. These findings raises the pivotal question of whether cancer risk related to primary epimutations may be limited to *BRCA1* as a single gene, or similar mechanisms may affect other genes enhancing the risk of other cancer types. The answer to this question is of huge importance to our understanding of the potential role of intrauterine events to cancer risk.

Second, in case we detect normal tissue epimutations in *MGMT* to be associated with incidental cancer risk, that will add important information to our understanding of cancer-initiating events in general. The fact that germline mutations in the *TP53* gene in the Li-Fraumeni syndrome, *BRCA1/2* germline in breast / ovarian cancer families and *MLH1/MSH2* mutations in families with colon cancer are associated with high tumor risk confirms mutations in these genes to be initial triggering events in the carcinogenic process among these patients. On the other hand, *TP53* mutations are known also to arise as somatic events later during cancer evolution (97, 98), and epimutations in general are considered of somatic origin. Thus, information revealing that epimutations are not always late/somatic but occur at the embryonic stage and confer cancer risk later in life, will provide important information for a better understanding of the role of key driving mutations and epimutations during cancer evolution in these organs.

Finally, a significantly increased risk for distinct cancer forms among methylation carriers may question the potential for selective screening of these individuals. The prognosis of colon cancer, in particular, relies on early diagnosis, and the debate of selective colonoscopy-screening is ongoing.

**The Women Health Initiative (WHI) is a unique study with a unique biobank,** including normal tissue DNA from > 160.000 American women followed over 3 decades for incidental diseases, including cancers, with detailed information including histopathological confirmation of diagnosis. In collaboration with the WHI, we already have completed one successful study of mosaic gene methylation (*BRCA1*) as a predictor for subsequent incident cancers (main WHI investigator: [name]).

**Laboratory analytical methods.** The laboratory methods previously applied for promoter methylation studies have been suboptimal with respect to sensitivity as well as precision. None of the methods applied, including recent pyrosequencing (limited by short read lengths with limited sensitivity), could depict exact methylation pattern across individual cells (Figure 1), and methylation arrays, like the Illumina 450k, are restricted to cover only a limited number of CpGs across each promoter region.

To overcome these obstacles, we have developed a novel highly sensitive NGS-based assay, allowing detailing methylation patterns across individual cells (99). This assay has been customized, covering the individual genes needed for each analysis. This will allow high-

throughput analyses (96 samples on each of our two MiSeq instruments at any given time), yielding allele specific methylation calls at very high depth (25.000x).

**Bioinformatics.** Multiple bioinformatic tools for analysis of differential DNA methylation are available, however none of them account for potential existence of epialleles within a sample. To address their limitations we have developed a set of epiallele-aware bioinformatic tools, which are publicly available and can be easily employed by the scientific community. Among them, a method for discovery of low-frequency, low-magnitude aberrant methylation events in methylation array and next-generation sequencing data [<https://github.com/BBCG/ramr>, <https://www.biorxiv.org/content/10.1101/2020.12.01.403501v1>], and set of methods allowing to call hypermethylated epiallele frequencies at the level of genomic regions or individual cytosines, as well as to test the significance of the association between epiallele methylation status and single nucleotide polymorphisms (SNPs) [<https://github.com/BBCG/epialleleR>]. Recently, all details about our assay determining promoter methylation status of *MGMT* and *BRCA1* in the same run has been published and is openly available (100). Special focus during implementation of these methods was given not only to the functionality but also to their performance, resulting in excellent data processing speed, scalability and readiness to high-coverage whole-genome datasets.

### Power analysis determining number of participants.

We will analyze *MGMT* promoter methylation in WBC samples collected at study inclusion from incident cases of colon cancer, glioblastomas and high-grade diffuse B-cell lymphomas and in matched controls drawn from the WHI biobank in a nested case-control design. With respect to **statistical power**, in preliminary analyses, measuring *MGMT* WBC methylation in umbilical cord blood from girls in the Norwegian Mother and child study (MoBa), we found WBC *MGMT* methylation in 197/1260: 15.6% of newborn girls (95% CI: 13.7 -17.8%). From mothers (age 20-40), *MGMT* methylation was revealed among 100/575; 17.3.% (CI: 14.4-20.7%).

While some evidence indicates that *MGMT* methylation may occur more frequently in right- as compared to left-sided colon cancers (101), this is not firmly established. On the other hand, there is no evidence indicating *MGMT* methylation may occur at a higher frequency in left-sided colon cancer or rectal tumours as compared to right-sided / transversal cancers. Taking into account the biological differences between right- versus left-sided colon cancers, for this study, we will analyse *MGMT* methylation status in right-sided and left-sided colon cancers separately.

We will use our preliminary data for methylation / SNP rs16906252, obtained from young adults, as basis for estimates of statistical power. A modest correlation between the rs16906252 and promoter methylation has been reported previously (86, 87, 89, 92, 102). In our data set, among 575 individuals, 35 were methylated carrying the variant allele (6.1%), 49 carried the variant allele without *MGMT* methylation (8.5%), 65/575 were homozygous for the reference rs16906252 allele carrying *MGMT* methylation (11.3%), while 426/575 (74%) were homozygous for the reference allele and did not carry *MGMT* methylation.

The figures above allow testing potential effects of the SNP allele and *MGMT* methylation separately on colon cancer risk. For both tests, we assume a HR of at least 2.

**Testing for the effect of *MGMT* methylation status among individuals not carrying the SNP variant.** Removing all carriers of the SNP rs16906252 variant allele (among young women 84/575; 14.6%), less than 20% of participant in total will be omitted from the statistical analysis. In the group homozygous for the reference rs16906252 allele 65/491 carry *MGMT* methylation (13.2%). For a 1 : 2 matched nested case control design assuming a HR of 2 and

assuming a methylation frequency of 12% we will need 195 cancer patients (Table 1). Assuming a methylation frequency of 8%, this number increases to 310. Assuming up to 20% of all individuals to be either homo- or heterozygous for the variant allele, another 66 patients need to be added. Accounting for some samples being lost to analytical failure, starting with  $n = 400$  patients with 800 controls in a 1 : 2 design will provide an adequate sample size.

**Testing for the effect of *MGMT* variant allele status among individuals not carrying *MGMT* promoter methylation.** Out of 575 individuals, in total 100 were found methylated at the *MGMT* promoter (17.4%). Among the non-methylated individuals (82.6%; 475/575), 10.3%; (49/475) had the variant allele. Assuming the variant allele to be found among 8% (or more) of individuals, the calculations above will apply, confirming a total of  $n = 400$  patients and 800 controls will be adequate for this test as well.

Taken together, we are able to test for the effect of *MGMT* methylation and the variant rs16906252 allele separately in nested case-control cohorts of 400 patients and 800 controls in a robust design. Thus, we aim testing for potential impact of *MGMT* methylation status and the rs16906252 variant allele on HR for right- and left-sided colon cancer (2 separate cohorts) with 400 patients and 800 matched controls for each comparison.

The fact that glioblastoma is a less common cancer form does not exclude constitutional *MGMT* methylation as a potential risk factor. As for glioblastomas, in the WHI study a total of  $n = 195$  glioblastomas are so far recorded. Assuming a methylation frequency in the normal population of between 12 and 15% and a cancer OR of 2, a potential impact of *MGMT* promoter methylation may be tested in the total group with a power of 0.9 (Table 1), and the impact of *MGMT* methylation and rs16906252 variant allele status separately with a power between 0.8 and 0.9, assuming a 1 : 4 nested control design.

Considering diffuse large cell B-lymphomas, the WHI contains more than 500 cases. With the *MGMT* methylation frequencies recorded in the literature, we assume a HR and statistical power calculation resembling that performed for each of the two colon cancer groups. Thus, we will enroll  $n = 400$  lymphoma cases with 800 matched controls.

**Table 1.** Overview of sample sizes required given  $\alpha = 0.05$ ,  $1-\beta = 0.8$  or  $0.9$ , and OR in the range of 1.3 – 3.0, for different percentages of methylated healthy individuals (controls) in the population. The numbers listed are given as the number of cancer cases required, given a 1:2 matched design (2 healthy controls per analyzed cancer case) or a 1:4 matched design

| HR  | Power ( $1-\beta$ ) | Match 1 : 2 |      |      | Match 1 : 4 |      |      |
|-----|---------------------|-------------|------|------|-------------|------|------|
|     |                     | 8 %         | 12 % | 15 % | 8 %         | 12 % | 15 % |
| 1.5 | 0.8                 | 780         | 490  | 375  | 604         | 378  | 290  |
| 1.5 | 0.9                 | na          | 650  | 500  | 783         | 483  | 377  |
| 2.0 | 0.8                 | 230         | 145  | 112  | 186         | 115  | 87   |
| 2.0 | 0.9                 | 310         | 195  | 150  | 236         | 147  | 111  |
| 3.0 | 0.8                 | 75          | 47   | 35   | 62          | na   | na   |
| 3.0 | 0.9                 | 100         | 62   | 45   | 77          | na   | na   |

**Summary of individuals to be enrolled.** Based on the estimates above, for the colon cancer study we need to enroll a total of  $n = 800$  participants with colon cancers and a total of  $n = 1.600$  controls. For the glioblastoma study, we will enroll all 195 participants developing glioblastomas with  $n = 780$  controls, while for the lymphoma study 400 cases and 800 controls will be included. **This adds to a total number of 4.575 individuals.** However, like for the previous *BRC1* study, we assume several control individuals may act as controls in different comparisons; thus, most likely this number of control individuals may be reduced. In our previous study on breast- and ovarian cancers (WHI AS543), we were able to reduce the total number of controls by about 23% by using some of the same controls for both comparisons. As

for this study, we like to keep separate controls for the two colon-studies. However, leaving one of these out, assuming a reduction of controls of 20% among the rest, we may limit the number of controls by 476; thus, the total number of samples should be around 4.100.

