### **Statistical analysis of data.**

The potential association between methylation and risk of cancer will be performed by Cox multivariate analysis as the primary analysis. In addition, for sensitivity analysis we will perform logistic regression analysis. In both analyses, potential confounding variables will be included as co-variables, similar to our WHI AS543 study now in revised review in JAMA Oncology. The co-variables included will include age, race, previous hormone usage, DNA extraction method and geographical location. Methylation positivity for each sample will be determined based on presence fully methylated alleles (VEF), and the laboratory analysis conducted blinded to case control identity. Optimization of cutoff values will be performed using R package OptimalCutpoints (v1.1-4).(100).

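### The lymphoma cohort has no minimum interval from blood draw to diagnosis, so circulating preclinical tumour cells could inflate its association with WBC methylation

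*Protocol*

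**What the plan says.** All statements are from the protocol.

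- **Samples and cases.** The power section takes "WBC samples collected at study inclusion from incident cases of colon cancer, glioblastomas and high-grade diffuse B-cell lymphomas", with matched controls from the same biobank. For lymphoma it plans 400 cases and 800 controls and says that more than 500 cases exist. It does not say how the 400 are chosen.
- **Analysis.** Under the statistical analysis heading, the association "will be performed by Cox multivariate analysis as the primary analysis", and "for sensitivity analysis we will perform logistic regression analysis". On adjustment: "The co-variables included will include age, race, previous hormone usage, DNA extraction method and geographical location". None of these concerns time from draw to diagnosis.
- **Exposure.** A sample is positive when fully methylated alleles are present, with an optimised cutoff. The laboratory section gives a depth of 25,000x.
- **The bias and the precedent.** The evidence section introduces the earlier prospective BRCA1 work with "To avoid the bias of tumor-related effects on WBC methylation". It reports that the association held "even in sub analyses limited to women developing their cancers >5 years after WBC sampling".
- **Tumour methylation.** For diffuse large B-cell lymphoma, "between 20 and 40% of the tumors have been reported methylated" for MGMT.

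**The concern.** Blood drawn before diagnosis is not necessarily blood drawn before disease. In a woman diagnosed soon after the draw, a preclinical tumour may already be present. For colon cancer and glioblastoma this matters less, because the tumour is not of blood-cell lineage. For lymphoma the sampled tissue contains the tumour's own lineage, and the tumour often carries the very mark that defines exposure. A circulating clone could then make the sample positive.

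Blinding, matching and the listed covariates do not remove this, because the signal would really be in the cases' blood. Logistic regression would show the same bias as the Cox model.

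At stake is the interpretation of the lymphoma result. The study aims to show that constitutional methylation precedes and predicts cancer. Lymphoma is also the mesodermal member of the three-germ-layer argument. Without a lag, the stated analyses cannot separate constitutional risk from early disease.

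**Working it through.** The plan gives no figure for this bias, so there is none to reproduce. The check has two parts: the possible size of the bias, and the cost of restricting cases.

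**1. Size under a true odds ratio of 1**

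Inputs:
- p0, control positivity: 12%, one of the plan's Table 1 values.
- m, share of tumours methylated: 20 to 40%, from the protocol.
- f, share of lymphoma cases with preclinical disease at the draw: 5 to 20%, *assumed*.
- c, share of methylated preclinical tumours that turn the sample positive: 50 to 100%, *assumed*.

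Formulas: case positivity p1 = p0 + (1 − p0) × f × m × c; apparent OR = [p1/(1 − p1)] / [p0/(1 − p0)]. The last column is the chance of a significant result in the risk direction with 400 cases and 800 controls (unmatched two-proportion approximation, two-sided 0.05, so 2.5% nominal).

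| f | m | c | p1 | Apparent OR | False positive |
|---|---|---|---|---|---|
| 0.05 | 0.20 | 0.50 | 0.12 + 0.88 × 0.005 = 0.1244 | 1.04 | 4% |
| 0.10 | 0.30 | 0.50 | 0.12 + 0.88 × 0.015 = 0.1332 | 1.13 | 10% |
| 0.10 | 0.30 | 0.75 | 0.12 + 0.88 × 0.0225 = 0.1398 | 1.19 | 17% |
| 0.20 | 0.40 | 1.00 | 0.12 + 0.88 × 0.08 = 0.1904 | 1.72 | 89% |

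At 15% control positivity the largest value is 1.58. At 12 to 15%, the bias alone does not reach 2. Only at the plan's most cautious 8%, with every other input at its upper bound, does it touch that value: p1 = 0.08 + 0.92 × 0.08 = 0.1536, OR = (0.1536/0.8464)/(0.08/0.92) = 2.09. The protocol's own data put positivity higher, at 13.2% among women without the variant allele.

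**2. Cost of restricting cases**

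Table 1 asks for 310 cases (8% exposed) or 195 (12%) for 0.9 power at a ratio of 2 with 1:2 matching. The usual two-sided two-proportion formula gives 335 and 241. That mismatch is a separate matter. The powers below come from the formula, not from Table 1 (OR 2, 1:2, two-sided 0.05).

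| Cases analysed | 8% exposed | 12% exposed |
|---|---|---|
| 400 | 0.94 | 0.985 |
| 360 (10% removed) | 0.92 | 0.98 |
| 320 (20% removed) | 0.89 | 0.96 |
| 256 (20% removed, then 20% variant carriers set aside) | 0.815 | 0.92 |

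If exactly 500 cases were available, up to 500 − 400 = 100 (20%) could be early and 400 later cases would still remain. How many are early is not stated.

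**The case against.** The best case against has five parts.

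- **Silence is not a decision.** A time-to-diagnosis analysis could sit in an unseen SAP, and the protocol does not call its list of analyses complete. This stands for the sensitivity analysis. It does not answer case selection, because the protocol settles the number of lymphoma cases and sets no lag. Early cases drawn and assayed now can be excluded later only at the cost of sample size.
- **The main remedy is already used.** Blood is taken before diagnosis, as in the earlier study. This is true, and what is left is a residual bias. But that study also looked beyond 5 years.
- **The size rests on assumptions.** This stands. Neither f nor c has a source in the documents, and depth alone does not establish detection, since the cutoff may leave a few methylated reads below positivity. If diagnoses were spread evenly over 30 years (an assumption; the protocol mentions three decades of follow-up), 2/30 = 6.7% would fall within two years. Taking all of these as preclinical, with m = 0.30, gives an OR of 1.13 at c = 0.75 and 1.08 at c = 0.50.
- **Stronger readings go too far.** A reader might infer that every incident lymphoma case is taken, or that a check was deliberately dropped. The text says neither: it takes 400 of more than 500 without a selection rule, and the 5-year analysis is reported only as a sub-analysis of another study.
- **The argument is specific to lymphoma.** This stands. It does not carry over to the colon cohorts or to glioblastoma, where all 195 cases are enrolled and none are spare.

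**Conclusion.** The point holds for the lymphoma cohort. Followed as written, the protocol could report an association partly caused by preclinical disease, and its stated analyses could not tell this apart from constitutional risk.

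The size is unknown. At 12% control positivity a true odds ratio of 1 could appear as about 1.04 to 1.7, and mid-range inputs give about 1.1 to 1.2. The top of the range needs every input at its upper bound. Even the mid-range values would raise the false-positive rate in the risk direction from 2.5% to roughly 10 to 17%. These figures depend on the assumed shares of preclinical and detectable disease.

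A reader might conclude that a lymphoma odds ratio of 2 could be wholly artefact, or that the whole three-cancer conclusion is unsafe. The documents support neither: at the positivity the protocol observed, the bias alone stays below 2, and the mechanism concerns lymphoma only.

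**What to change.** 1. When drawing the 400 lymphoma cases, prefer those diagnosed beyond a lag fixed in advance, as far as the more than 500 available allow. The sponsor should choose the length and record the reason before samples are pulled.
2. Prespecify a lymphoma analysis restricted to cases diagnosed more than 5 years after the draw, with their matched controls.
3. State that a constitutional-risk conclusion for lymphoma depends on the association persisting in that analysis.

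The cost is one selection rule and one analysis. The restricted analysis will have fewer cases and wider intervals. Some power may also be lost in the main lymphoma analysis if too few cases lie beyond the lag; the draw-to-diagnosis distribution should be tabulated first, since a promise of no loss cannot be made without it. A 20% reduction from 400 cases still leaves about 0.89 power at 8% exposure and 0.96 at 12%, for an odds ratio of 2.
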